### Randomisation and masking

#### Sequence generation

A computer-generated randomisation list will be prepared by an independent statistician at London School of Hygiene and Tropical Medicine (LSHTM), who will hold the sequence, will not be masked, and will not be involved in any other aspect of the trial. The sequence is in a 1:1 allocation ratio of CHX to NATA, with a random block size (2, 4 or 6).

#### Allocation concealment and implementation

The randomisation sequences will be concealed in sequentially numbered, opaque envelopes. The envelopes will be prepared by a person independent of all other aspects of the trial. The randomisation administrator (nurse or pharmacist) will conduct the random allocation procedure. The investigational products will be stored in the trial coordination office in a locked and separate drug cabinet dedicated for this clinical trial only. The cabinet will only be used for drug storage and will only be accessed by the randomisation administrator. The randomisation administrator will work in a separate room in the clinic. After the patient has been recruited and assessed, they will be guided to this separate room where the randomisation allocation will be conducted.

#### Masking

The topical treatments being compared in this trial have a different appearance: the CHX 0.2% is a clear, colourless solution and the natamycin 5% is an opaque, white suspension. Therefore, it is not possible to mask the participants to this difference in visual appearance. However, the patients will not be told which treatment they have been allocated. Prior to any follow-up clinical examinations, a nurse, otherwise uninvolved in the study, will wipe away any white natamycin residue from the patient’s eyes to avoid unmasking the clinical assessor. This procedure was used successfully in other trials.^6^ All clinicians involved in the clinical assessment of the patients will be masked to the allocation. The statistician who will perform the primary analysis will be masked to the allocation and only receive the actual allocation code sequence from the independent statistician after the analysis code has been prepared and pre-tested with a test sequence. The primary outcome is visual acuity at 3 months assessed by an optometrist who will not have been involved in any other aspects of the trial and masked to the allocation. By 3 months, the treatment courses are likely to be completed. There will be masked grading of the photographs to independently confirm outcome measures and assess for any systematic bias on the part of the clinical examiners.

#### Unmasking

Unmasking is a serious action and should only be performed if necessary to ensure the safety of a study participant. Anyone unmasked to randomised treatment for the purpose of creating analyses for independent data and safety monitoring committees will not be involved in any other aspects of the conduct or final analysis of the study. A list will be maintained of all unmasked members of staff and will be approved by the chief investigator. Such staff members must sign a document to indicate that they are aware of their responsibilities with respect to confidentiality. The processes used to provide access to unmasked treatment codes and reports relating to these codes shall be documented.

### Intervention and treatment

The standard of care in this hospital is for cases of FK to be admitted. If willing, patients will be admitted for close observation and supervised treatment, until there are signs of improvement and the supervising clinician considers it safe to provide ongoing management on an outpatient basis.

#### Trial treatment arms

CHX 0.2% w/v eye-dropsCHX 0.2% w/v solution, as eye-drops, will be applied to the surface of the infected eye (one drop per application). The CHX 0.2% w/v eye-drops used in these studies is produced by Mandeville Medicines, UK.Natamycin 5% eye-dropsNatamycin 5% w/v suspension, as eye-drops, will be applied to the surface of the infected eye (one drop per application). Topical natamycin 5% is produced by FDC Pharmaceuticals, India.

#### Dosing schedule

Both trial treatment arms will follow the same dosing schedule. Eye-drops will be given hourly day and night for 48 hours, then hourly while awake for 5 days, and then 2 hourly while awake for two further weeks. If the ulcer has healed (epithelial defect less than 1 mm, infiltrate resolved, with or without corneal scarring), then treatment is stopped. If resolving stromal infiltration and/or epithelial defect >1 mm but <5 mm, treatment is reduced to four times daily. If resolving but with epithelial defect >5 mm and/or stromal infiltration/hypopyon, treatment is reduced to six times daily. Treatment duration will be tailored to clinical response, with patients reviewed regularly while on treatment in addition to their scheduled study visits.

#### Topical treatments

Several other topical medicines are used in the standard care of people with corneal infections:

Fluorescein sodium ophthalmic strips (Contacare Ophthalmics and Diagnostics, India) to highlight the area of cornea epithelial defect.Anaesthetic eye-drops to anaesthetise the cornea before procedures such as microbiology samples: Proxymetacaine 0.5% eye-drop Minims (Bausch and Lomb, UK).Antibiotic eye-drops may be used as per the judgement of the treating ophthalmologist if there is a suspicion of mixed bacterial and FK: Moxifloxacin 0.5% eye-drops (Centaur Pharmaceuticals, India).Mydriatic eye-drops for pupil dilation to reduce discomfort from the infection: cyclopentolate 2% eye-drops (Aurolab, India), three times a day.Ocular hypotensive eye-drops if the intraocular pressure is elevated >25 mm Hg. This will be at the discretion of the supervising clinician; usual first line treatment is timolol 0.5% eye-drops (Allergan, India).

#### Ancillary treatment in patients refractory to trial medication

In patients with progressive FK despite 7 days or more of trial medication, additional treatment options will be considered and offered. After repeating microbiological tests to rule out a mixed bacterial infection, deteriorating patients are started on topical voriconazole 1% hourly if the ulcer is superficial only. For ulcers that are deeper than 75% of the corneal thickness, oral ketoconazole 200 mg two times a day is added (with monitoring of liver function). The choice of ancillary treatment is due to local availability. If, following 7 days of additional treatment, despite these measures there is ongoing progression, surgical management such as a TPK can be considered.

#### Non-pharmacological treatment

It is sometimes necessary to perform surgical procedures during the management of corneal infections. In the context of the trial these will be performed by the supervising consultant ophthalmologist. These can include:

Insertion of a bandage contact lens for very small perforations.Tissue glue and patch for small perforations.Corneal transplant (TPK) for progressive fungal infections that are refractory to medical management or large perforations.Conjunctival flaps to cover corneas in non-healing ulcers.

### Outcome measures

#### Primary outcome measure

The primary outcome will be BSCVA in logMAR units at 3 months. This will be measured by a trial-certified optometrist, independent of all other aspects of the study and masked to allocation. This has been the primary outcome of several other trials and will therefore facilitate comparison. Three months is the time at which clinical experience suggests most corneal ulcers have usually healed. BSCVA is chosen as it is easy to measure and is of functional significance. We will measure the BSCVA using an LED-backlit, Tumbling-E LogMAR chart (Good-Lite, Illinois, USA) under controlled conditions. We will also measure vision using Peek Acuity, a validated smartphone application, in situations where the patient is unable to attend the hospital for follow-up and outcome data is only available through a domiciliary visit.^29^ For patients who have counting fingers (CF) vision or less, predefined logMAR values will be assigned based on previous clinical trials.^30 31^ Similarly, for patients who undergo a corneal transplant (TPK), a predefined visual acuity of 1.9 logMAR will be given, or last observation carried forward (whichever is the better vision), as per previous studies.^6^

#### Secondary outcome measures

We will be assessing a number of secondary outcome measures that relate to different measures of visual acuity such as Peek Acuity; clinical signs of healing such as reduction of epithelial defect; microbiological culture rates and other clinical outcome measures such as scar size or perforation rate. These secondary outcomes together with their analyses are outlined in the Analysis Plan section.

### Outcome assessments

Participants will be reassessed at 2 days, 1 week, 2 weeks, 3 weeks, 2 months and 3 months following enrolment. Additional examinations, outside the trial protocol schedule may be conducted by the supervising clinician as indicated. The specific assessments to be carried out at each visit are indicated in table 3. These will be conducted in the same way described for the baseline assessment as described (table 2). At each follow-up assessment, the participant will be asked about adherence to treatment and symptoms, including side effects, if still receiving trial treatment. This will be recorded in the case record file. To monitor trial medication adherence, the study participants will be asked to bring their eye-drop bottles to the 1-week, 2-week and 3-week follow-ups. The amount of remaining medication will be measured by weighing the bottle and will be compared with the anticipated remaining amount provided the drops were being used as instructed, resulting in a ratio of actually remaining to what is anticipated. Participants will be resupplied with medication as needed. The presenting visual acuity will be measured on each visit. In addition, the BSCVA will also be measured at the 3-month follow-up (primary outcome measure). At the final 3-month follow-up, the three quality of life questionnaires will be repeated. On each occasion the eyes will be examined using a slit-lamp and the cornea photographed. The IVCM will be repeated at 1, 2 and 3 weeks to determine whether there is evidence of fungal hyphae resolution with the fragmentation of linear elements. At the 1-week follow-up if the ulcer has not healed it will be rescraped for repeat culture to determine whether the keratitis is now culture positive or culture negative. We will give the study participants appointment cards for the next follow-up and they will be reminded about the follow-up a week prior to the date. Public transport costs will be paid for participants who are outpatients.

**Table 3 T3:** Baseline and follow-up assessment components

Assessment item	Baseline	Day 2	Day 7	Day 14	Day 21	Day 60	Day 90
History/baseline questionnaire	X						
Check treatment adherence		X	X	X	X	X	X
Check for side effects		X	X	X	X	X	X
Visual acuity—presenting	X	X	X	X	X	X	X
Visual acuity—BSCVA	X						X
Contrast sensitivity	X						X
Slit-lamp examination	X	X	X	X	X	X	X
Cornea photography	X	X	X	X	X	X	X
In vivo confocal microscopy	X		X	X	X		
Cornea samples (microbiology/PCR)	X		X				
Quality of life tools	X						X

BSCVA, best spectacle corrected visual acuity.

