### Treatment review

At each follow-up visit, participants will be reviewed by an ophthalmic clinician experienced in the management of FK. Clinical responses to antifungal therapy tend to be relatively slow (compared with bacterial infections). Prolonged topical treatment courses of 4–6 weeks are usually needed. Therefore, a change in therapy is usually not made for at least the first week. Other interventions may be indicated such as application of glue to corneal perforations, conjunctival flaps or TPK (corneal transplant).

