### Monitoring for harm

Patients will be monitored at each visit for adverse events or reactions. We will follow standardised definitions for adverse events, adverse reactions, unexpected adverse reactions, serious adverse events or reactions, and suspected unexpected serious adverse reaction. These, along with the reporting scheme, are given in online supplementary appendix 2.

10.1136/bmjopen-2020-038066.supp2Supplementary data

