Perforation and/or TPK and/or conjunctival advancement by 3 months (slit lamp examination by ophthalmic clinician)	The number of patients who undergo perforation and/or require TPK and/or have undergone conjunctival advancement by 3 months will be reported using CIs and descriptive statistics. The study is not powered to detect a difference in perforation rate or TPK between treatment groups; not reporting a significant difference may be wrongly interpreted as there being no difference between groups. We will therefore perform an exploratory analysis to compare TPK or perforation rates between treatment groups. This will be by logistic regression to compute an OR by arm.
Loss of eye	The number of patients who have their eye surgically removed (evisceration or enucleation) during the 3 months follow-up period will be reported using CIs and descriptive statistics in the same way as for TPK/perforation rate above, along with exploratory analysis using logistic regression to find risk factors for eye loss and OR for this by arm.
Ocular adverse effects, slit lamp examination by ophthalmic clinician	The proportion of patients with one or more adverse events will be compared using Fisher’s exact test. Additional analysis to compare the rate of adverse events during the 3 months follow-up will be by Poisson regression as this can take into account multiple instances within one participant.
QoL assessed using: EQ-5D, WHO/PBD-VF20, WHOQOL-BREF	QoL can be assessed quantitatively using different tools depending on what is of interest. For example, disease-related QoL can be assessed (eg, vision related QoL, VRQoL) or more general health-related issues irrespective of the disease can be investigated (health-related QoL, HRQoL).^40^
	We will use the WHO/PBD-VF20 (WHO/ Prevention of Blindness and Deafness—Visual Functioning 20-item questionnaire) VRQoL tool. This tool measures the impact of visual impairment in the person’s life including mental well-being, dependency and social functioning. These have been used in a number of other visual related studies to show a difference in QoL.^36 37^

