	2. Pin-hole visual acuity in logMAR at 3 months, trial-certified optometrist
	3. Scar/infiltrate size at 1 week, 3 weeks and 3 months (slit-lamp examination by ophthalmic clinician)
	4. Ulcer depth at 1 week and 3 weeks (slit-lamp examination by ophthalmic clinician).
	5. Hypopyon height at 1 and 3 weeks, (slit-lamp examination by ophthalmic clinician).
	6. Perforation and/or TPK by 3 months (slit-lamp examination by ophthalmic clinician).
	7. Positive culture rate at 1 week
	8. Ocular adverse effects at each follow-up visit (day 2, day 7, day 14, 3 weeks, 2 months, 3 months), slit-lamp examination by ophthalmic clinician
	9. Quality of life (QoL) assessed using: EQ-5D, WHO/PBD-VF20, WHOQOL-BREF (comparison between baseline and QoL measures at 3 months)
	10. Cost-effectiveness analysis, using EQ-5D data from 3 months and direct cost data
	11. Drug adherence at each follow-up visit (day 2, day 7, day 14, 3 weeks, 2 months, 3 months) while the patient is using study medications

EQ-5D, EuroQol-5 Dimension; LMIC, low-income and middle-income countries; MK, microbial keratitis; TPK, therapeutic penetrating keratoplasty.

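### The patient enquiry about side effects is limited to those still on trial drug, in conflict with the every-visit adverse-event monitoring stated elsewhere, so symptoms after treatment stops may go unasked

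*Protocol article*

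**What the plan says.** All places are in the protocol article.

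- **Outcome assessments** sets the visits: "Participants will be reassessed at 2 days, 1 week, 2 weeks, 3 weeks, 2 months and 3 months following enrolment". At each one, "the participant will be asked about adherence to treatment and symptoms, including side effects, if still receiving trial treatment", and the answers go into the case record. This is the only sentence in the article that describes how symptoms and side effects are elicited from the patient.
- The same section says "The specific assessments to be carried out at each visit are indicated in table 3". **Table 3** marks the row "Check for side effects" at all six follow-up visits, including Days 60 and 90. It marks the treatment-adherence row at the same six visits.
- **Monitoring for harm**: "Patients will be monitored at each visit for adverse events or reactions". No on-treatment condition is attached.
- **Table 5**, key secondary outcome 8: "Ocular adverse effects at each follow-up visit (day 2, day 7, day 14, 3 weeks, 2 months, 3 months), slit-lamp examination by ophthalmic clinician". Again there is no condition. Item 11, drug adherence, does carry one: it applies only while study medication is in use.
- **Treatment review**: "Prolonged topical treatment courses of 4–6 weeks are usually needed".
- **Stopping rules** keeps a patient whose medication is stopped on the scheduled follow-up examinations.
- **Table 4**, ocular adverse effects, compares the proportion with any event by Fisher's exact test and adds: "Additional analysis to compare the rate of adverse events during the 3 months follow-up will be by Poisson regression".

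**The concern.** The article gives two rules for the same enquiry. One asks about side effects only while the patient is on trial drug. The other looks for adverse events at every visit to 3 months. A site has to choose, and the narrower rule is the one written as an instruction on what to ask.

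Under the narrower rule two kinds of information are at risk. The first is symptoms that arise late in the course, between the last on-drug visit and the end of treatment; a patient already off drug at Day 60 would not be asked about them. The second is the course of a reaction that led to stopping: the patient still attends, but nothing in that sentence has anyone ask whether it resolved.

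Time on drug is not fixed by design. Under Dosing schedule it depends on healing, and under Stopping rules it can end because of an adverse event. The number of enquiries per patient could therefore vary for reasons connected with treatment, while Table 4 analyses events over a common 3-month window.

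**Working it through.** The plan states no figure for the share of a course covered by side-effect enquiry, so there is none to reproduce. The check has two parts.

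**1. The passages side by side**

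| Place | What is ascertained | On-treatment condition? |
|---|---|---|
| Outcome assessments, text | Adherence, symptoms, side effects (asked) | Yes, one clause covering the enquiry |
| Table 3, side-effect row | Side effects, six visits | None stated |
| Table 3, adherence row | Adherence, six visits | None stated, but necessarily conditional |
| Monitoring for harm | Adverse events or reactions, each visit | None |
| Table 5, item 8 | Ocular adverse effects by slit lamp, each visit to 3 months | None |
| Table 5, item 11 | Adherence, each visit | Yes |

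Table 3 points towards an unconditional check but does not settle the matter. Its adherence row carries the same six marks, and adherence cannot be checked once treatment has ended. Table 5 item 11 confirms this by listing the six visits and adding the condition. A mark in Table 3 is therefore compatible with a condition, and the text applies a single condition to adherence and side effects together. The clear conflict is with Monitoring for harm and Table 5 item 8.

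**2. How much of a course follows the last on-drug visit**

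Inputs: visits at Days 2, 7, 14, 21, 60 and 90 (Table 3); courses of 28 to 42 days (Treatment review). For any such course the last scheduled visit on drug is Day 21, and Day 60 falls 60 − 42 = 18 to 60 − 28 = 32 days after treatment ends.

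Share in calendar days = (course length − 21) / course length:

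- 4 weeks: 7/28 = 25%
- 5 weeks: 14/35 = 40%
- 6 weeks: 21/42 = 50%

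By number of drops the share is smaller, because dosing is heaviest early. Dosing schedule gives hourly drops for 48 hours, hourly while awake for 5 days, then 2-hourly while awake for two weeks. With h waking hours, drops to Day 21 = 24 × 2 + 5h + 14 × h/2. I assume h = 14 to 18. After Day 21 I assume 4 a day, 6 a day, or continued 2-hourly dosing; the first two are the reduced frequencies that the section names. At h = 16 the drops to Day 21 are 48 + 80 + 112 = 240.

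- 4 weeks, 4 a day: 28/(240 + 28) = 10.4%
- 4 weeks, 2-hourly (8 a day): 56/(240 + 56) = 18.9%
- 6 weeks, 4 a day: 84/(240 + 84) = 25.9%
- 6 weeks, 2-hourly (8 a day): 168/(240 + 168) = 41.2%

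Over h = 14 to 18 the full range is about 10% to 19% for 4 weeks and 24% to 42% for 6 weeks.

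If side effects are asked about at every visit whatever the treatment status, the share with no later scheduled enquiry is 0%, because Day 60 covers the period back to Day 21.

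**The case against.** The strongest reply is that the design already is an every-visit check. Outcome assessments defers to Table 3 for visit content, Table 3 marks the side-effect row at Days 60 and 90, and Monitoring for harm and Table 5 item 8 are unconditional. On this view one loosely worded clause is being set against the rest of the document. That stands in part: it rules out saying that the plan as a whole never asks after treatment ends. It does not remove the conflict, since the clause is the only instruction on questioning the patient and Table 3's marks are not self-evidently unconditional.

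Other replies also carry weight:

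- The Table 4 and Table 5 outcome is headed as slit-lamp examination, which takes place at every visit in both arms. Signs are therefore collected throughout, and the gap concerns symptoms only.
- Dosing schedule provides regular extra reviews while on treatment, which may catch some events between Day 21 and the end of the course. They do not reach the period after stopping.
- Adverse-event definitions and the reporting scheme are in a supplementary appendix that is not shown, and may say more.

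A reader might infer that patients who stop early leave ascertainment altogether, or that the less tolerated drug will look safer because its users are no longer asked. The documents do not support either. Stopping rules keeps these patients in follow-up with slit-lamp examination. A patient stopped for an adverse event has already had that event identified and so already counts in the Fisher comparison. No difference between arms in treatment duration is given, and no reporting rate per visit from which a bias could be computed.

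**Conclusion.** The inconsistency is real and worth correcting. The conditional clause in Outcome assessments conflicts with Monitoring for harm and Table 5 item 8, and fits poorly with Table 3. If sites follow it, symptom-based events that arise after Day 21, and the resolution of reactions that led to stopping, may not be elicited at Days 60 and 90, while the Table 4 comparison spans 3 months.

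The period concerned is 25% to 50% of a 4 to 6 week course in calendar days. This should not be read as a share of drug exposure: by number of drops it is about 10% to 42% across the dosing assumptions used. The figures rest on the usual course length that the article gives and apply only if the clause is followed as written. The direction and size of any effect on the comparison between arms cannot be established from the document.

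**What to change.** In Outcome assessments, attach the on-treatment condition to adherence alone, as Table 5 item 11 does. State that all participants, on or off trial drug, are asked at all six follow-up visits about symptoms and side effects since the previous visit, and record for each event whether the participant was on or off drug at onset. At Day 60 the question should reach back to Day 21. A footnote to Table 3 marking only the adherence row as conditional would remove the remaining ambiguity.

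The cost is one sentence and one case-record-form instruction, with no new visit and no change to treatment. Some events unrelated to the drug will be recorded after treatment ends; the on/off-drug record lets the analysis separate them. The Day 60 enquiry will rely partly on recall.
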